The total number of available diagnostic results will thus be: two Kato-Katz thick smears/sample, one FLOTAC apparatus with two different solutions/sample (total: three diagnostic test results/sample; six diagnostic test results at baseline). Kato-Katz thick smear slides and the FLOTAC are both read quantitatively.

*Randomization and drug dosage*

All participants with complete diagnostic results will be listed in ascending order according to their identification number, and the four different treatment options coded 1-4. A random sequence of 1s, 2s, 3s and 4s will then be generated, and aligned with the list of participants, thus assigning each individual a specific drug-dosage combination.

The drug dosage will be:

Daily albendazole dose: 400 mg (1 day or 3 days)

Daily mebendazole dose: 500 mg (1 day or 3 days)

For each participant, an identical envelope labeled with his/her name and containing the appropriate drugs according to the assigned treatment will be prepared.

*Treatment procedures, drug dosage and application*

Upon completion of the baseline parasitological survey, all participants with complete diagnostic results and ≥1 STH infection will be invited for treatment. They will be informed again about the treatment procedures, asked not to drink alcohol on treatment days, and to disclose their health and pregnancy status prior to treatment. On the days of treatment, teams of local health personnel and study team members will visit the participants individually in their houses after dinner time, enquire about their health and pregnancy status, and distribute the allocated drugs together with bottled water. Drug intake will be directly observed. This procedure will be repeated two times for those participants allocated to triple-dose treatment.

*Safety assessment:* All participants will be interviewed regarding adverse events of the treatment 24 h after drug application using a detailed semi-quantitative questionnaire providing a grading system for reported symptoms (Appendix 3). A medical doctor will be permanently available to the participants for 24 h after drug application for immediate attention to any adverse drug-related events which will be described in detail on an individual basis.

*Sample collection and diagnostic procedures for follow-up parasitological survey*

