**Data analysis**

The species-specific cure rates in individual study arms will be compared using the χ2 test. For each individual, the arithmetic mean number of eggs per gram stool (EPG) before and after treatment and for each helminth species will be calculated based on the egg counts resulting from the different diagnostic tests. Subsequently, the geometric mean EPG for the different study arms will be calculated, and the fecal egg count reduction test employed to compare the achieved specie-specific egg burden reductions.

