**Sample size**

At least 370 individuals aged ≥5 years will be enrolled. Enrolment will be stopped once 400 individuals have signed up, even if additional volunteers are available. The calculated sample size is based on the following assumptions: A total of 176 individuals (44 in each of the four treatment arms) will be needed to demonstrate that single-dose albendazole is performing better than single-dose mebendazole for the cure of hookworm infections with 90% power using a 1-sided statistical test with an α-level of 0.05. The cure rates of albendazole and mebendazole are assumed to be 75% (76.4% in a recent meta-analysis of all published randomized placebo-controlled trials) and 45% (22.9%, multiplied by 2 to increase safety margin) (Keiser and Utzinger, 2008). To further increase the safety margin, the local prevalence of triple *A. lumbricoides*, *T. trichiura* and hookworm infections is assumed to be 60% (it was 76% during the study in 2006 (Steinmann et al., 2008a)), and the compliance is estimated to be 80%.

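### Free improvement: baseline egg counts are in hand before allocation, but the protocol uses them neither to stratify the randomisation nor to adjust the cure comparison

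*Protocol*

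**What the plan says.** **Allocation** (Protocol, Treatment and study procedures, Randomization and drug dosage). Everyone whose baseline stool results are complete is listed in order of identification number, and "A random sequence of 1s, 2s, 3s and 4s will then be generated, and aligned with the list of participants". No strata, block size or arm ratio is given. The list covers all such people, whereas only those with at least one of the three infections are later invited for treatment.

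**What is known by then** (same section). Kato-Katz slides are read within 45 minutes of preparation, and both Kato-Katz and FLOTAC give counts. FLOTAC may be read up to 12 weeks after collection. The requirement for complete results suggests that it too is available at allocation, but only Kato-Katz is certain.

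**Analysis** (Protocol, Data analysis). "The species-specific cure rates in individual study arms will be compared using the χ2 test". Baseline egg counts enter only the egg-reduction analysis.

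**Sample size** (Protocol, Sample size). "A total of 176 individuals (44 in each of the four treatment arms) will be needed" to show that single-dose albendazole beats single-dose mebendazole for hookworm cure, "with 90% power using a 1-sided statistical test with an α-level of 0.05". The assumed cure rates are 75% and 45%. Enrolment is 370 to 400.

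**The concern.** The chance of clearing all eggs plausibly falls as the baseline count rises. If it does, two things are given up.

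- **Balance.** Nothing in the text holds the number of hookworm-positive people, or their infection intensity, level across arms. Yet the sample size rests on "44 in each of the four treatment arms" for a hookworm endpoint.
- **Precision.** A prognostic variable that is already measured is left out of the test.

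The usual reason for avoiding blocks, that staff may guess the next assignment, carries little weight here because the list is complete before the sequence is generated. A statistical analysis plan could still add covariates, but it cannot stratify after allocation. The allocation half therefore belongs in this protocol.

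**Working it through.** **1. The plan's own figure.** Inputs from Sample size: p₁ = 0.75, p₂ = 0.45, one-sided α = 0.05 (z = 1.645), power 90% (z = 1.282). The mean rate is 0.60.

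n = [1.645·√(2·0.60·0.40) + 1.282·√(0.75·0.25 + 0.45·0.55)]² / 0.30² = (1.140 + 0.845)² / 0.09 = 43.8, so 44 per arm and 176 in total.

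Power at 44 per arm is 90.1%. Inflation: 176 / (0.60 × 0.80) = 367, against "At least 370 individuals aged ≥5 years will be enrolled". The plan therefore meets its target with the unadjusted test.

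**2. Arm sizes if the sequence is unrestricted** (an inference, since the text does not say). With 176 evaluable and probability 1/4 per arm, the mean is 44 and the SD is √(176 × 0.25 × 0.75) = 5.7.

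- The simulated 95% range is 33 to 55.
- The chance that at least one of the two single-dose arms falls below 38 is 25%.
- One-sided power at 33 versus 44 is 86%.
- Averaged over all draws, power is 89.7%, against 90.1% with equal arms. The loss is under 1 point.

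With 400 enrolled, 400 × 0.60 × 0.80 = 192 are evaluable. The range becomes 37 to 60 and the 25% falls to 7%.

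**3. Chance imbalance in intensity.** With 44 per arm, the difference between two arms in mean log egg count has SD √(2/44) = 0.21 (in SDs of log egg count). A difference above 0.25 SD occurs in 24% of trials, and above 0.5 SD in 2%.

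If the SD of log₁₀ EPG is 0.6 (assumed), the SD of the difference is 0.6 × 0.213 = 0.128. A gap of at least 0.2 log₁₀, about 1.6-fold in geometric mean, then occurs in 12% of trials. If the log-odds of cure fall by 1 to 2 per log₁₀ EPG (assumed), such a gap moves the observed cure difference by roughly slope × average p(1−p) × 0.2. That is 1 × 0.20 × 0.2 = 4 points, or 2 × 0.17 × 0.2 = 7 points, against a planned difference of 30.

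**4. Power with stratification and adjustment.** Simulation of 8,000 trials per setting, 44 per arm, marginal cure 75% versus 45%, one-sided α = 0.05. The odds ratio of non-cure per SD of log egg count is assumed.

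| Odds ratio per SD (assumed) | 1 | 1.5 | 2 | 3 | 4 |
|---|---|---|---|---|---|
| As written (unstratified, χ²) | 90% | 90% | 90% | 90% | 91% |
| Adjusted only | 90% | 90% | 92% | 94% | 96% |
| Stratified and adjusted | 90% | 90% | 93% | 95% | 97% |

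Type I error of the unadjusted test was 4.8% to 5.1%. The last row used close pairing on intensity, so a median split would capture only part of the small step from the second row to the third. The slopes of −1 and −2 in step 3 correspond to odds ratios per SD of e^0.6 = 1.8 and e^1.2 = 3.3, which lie inside this table.

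**The case against.** The strongest reply is that nothing here is wrong. Simple randomisation with a χ² test is a valid design, it reaches the stated power, and covariate adjustment is commonly left to the analysis plan. All of that stands. It makes this an improvement rather than an error, and the adjustment half is the weaker half. It does not remove the allocation half, which cannot be repaired later.

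A reader might infer more than the document supports:

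- **That the sequence is unrestricted.** The text neither states nor excludes blocking or equal totals. The 33 to 55 range depends on this reading.
- **That the trial will probably miss 44 per arm.** With exactly 176 evaluable, both single-dose arms reach 44 in only 23% of draws, but there 44 is simply the mean. The 60% is a deliberately lowered prevalence of triple infection, and hookworm prevalence cannot be below it. At the 76% seen in 2006, 370 to 400 enrolled give 370 × 0.76 × 0.80 = 225 to 400 × 0.76 × 0.80 = 243 evaluable. Both arms then reach 44 in about 95% to 99% of draws.
- **That power is 83%, or 77% at 33 versus 44.** Those are two-sided values, and the plan is one-sided.
- **That the comparison is confounded.** Chance imbalance under randomisation is covered by the test's error rate. It can shift one trial's estimate, but it is not bias.
- **That power is certainly lost.** At an odds ratio of 1 to 1.5 per SD there is essentially no gain.

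The mebendazole rate was also doubled as a margin. At the cited 76.4% versus 22.9%, one-sided power exceeds 99.9% even at 33 versus 44.

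**Conclusion.** The concern holds as a free improvement. The plan is valid and meets its stated 90% one-sided power at 44 per arm. Using the baseline counts would add 0 to about 6 points of one-sided power, and would protect the arm sizes and the intensity balance on which the hookworm comparison relies. If intensity does not predict cure, essentially nothing is lost.

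The size rests on an intensity–cure association and a spread of egg counts that the document does not give. The arm-size figures also rest on an unrestricted sequence and exactly 176 evaluable people.

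**What to change.** 1. **Allocation.** Once the list is complete, generate the sequence in blocks within three strata: hookworm-negative, and hookworm-positive below or above the median baseline Kato-Katz count. State the equal ratio and the block size. This adds no predictability, because no one joins the list after the sequence exists.
2. **Primary hookworm cure analysis.** Use logistic regression on arm and baseline log(EPG + 1), and report a standardised risk difference with its 95% confidence interval. Take EPG as the participant's mean count across tests, which the Data analysis section already defines. People positive only by FLOTAC, with a Kato-Katz count of zero, then still have a value.
3. **Supporting analysis.** Keep the χ² test as the unadjusted result.
4. **Other species.** Adjust the *A. lumbricoides* and *T. trichiura* cure comparisons for their own baseline log(EPG + 1).

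Cost: a few lines of code when the list is generated, and wording in the protocol and analysis plan. No extra participants, samples or tests are needed. Step 1 must be done before allocation; the rest can follow in the analysis plan, before outcome data are seen.

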**Risk/benefit assessment**

The study participants will benefit from free diagnosis and treatment of intestinal helminths. Adverse effects of anthelminthic treatment are uncommon. They include nausea, vomiting, and other transient gastro-intestinal symptoms. Severe adverse events are extremely rare.

**Data analysis**

The species-specific cure rates in individual study arms will be compared using the χ2 test. For each individual, the arithmetic mean number of eggs per gram stool (EPG) before and after treatment and for each helminth species will be calculated based on the egg counts resulting from the different diagnostic tests. Subsequently, the geometric mean EPG for the different study arms will be calculated, and the fecal egg count reduction test employed to compare the achieved specie-specific egg burden reductions.

**Sample size**

At least 370 individuals aged ≥5 years will be enrolled. Enrolment will be stopped once 400 individuals have signed up, even if additional volunteers are available. The calculated sample size is based on the following assumptions: A total of 176 individuals (44 in each of the four treatment arms) will be needed to demonstrate that single-dose albendazole is performing better than single-dose mebendazole for the cure of hookworm infections with 90% power using a 1-sided statistical test with an α-level of 0.05. The cure rates of albendazole and mebendazole are assumed to be 75% (76.4% in a recent meta-analysis of all published randomized placebo-controlled trials) and 45% (22.9%, multiplied by 2 to increase safety margin) (Keiser and Utzinger, 2008). To further increase the safety margin, the local prevalence of triple *A. lumbricoides*, *T. trichiura* and hookworm infections is assumed to be 60% (it was 76% during the study in 2006 (Steinmann et al., 2008a)), and the compliance is estimated to be 80%.

**Ethical considerations, data privacy, voluntariness, insurance**

Today, benzimidazole drugs are handed out to millions of people every year (Hotez et al., 2007), and medical ethics as well as the high burden resulting from STHs call for the consistent use of the most efficacious drug available. However, few rigorous studies assessing their efficacy have been published, and none are available which directly compare their safety and efficacy in a highly endemic setting and using a single-blind, randomized-controlled design (Keiser and Utzinger, 2008). In the frame of MDA campaigns, both drugs are administered to ≥2 year old individuals without previous diagnostic assessment or follow-up assessment of adverse events and treatment efficacy. The treatment of pregnant women is debated but pregnancy status is not commonly assessed before treatment (WHO, 2006).

All data collected within the frame of the study will be considered confidential and access restricted. During data analysis, individuals will only be identified using identification numbers, and neither names nor identification numbers will appear in any publications.

Participation in the study is strictly voluntary, and individuals not participating in the study will not experience any disadvantages. Full insurance coverage is provided by the institutional insurance covering the research activities of the STI.

**Appendix 3: Adverse event registration and grading sheet**
